## Abstract

**Background:**

The use of cardioplegia solutions as a myocardial protection technique is essential during cardiac surgery with cardiopulmonary bypass. The del Nido cardioplegia solution (DNS) has been widely used as a myocardial preservation technique for pediatric patients undergoing cardiac surgery with cardiopulmonary bypass. Its unique pharmacological features have created growing interest for adult cardiac surgery, especially for elderly patients or those with ventricular dysfunction who are more prone to ischemia-reperfusion injury. Ever since its implementation, several retrospective studies have been published to validate the efficacy, safety, and efficiency of DNS in adult patients undergoing coronary revascularization, valve replacement, or combined procedures. Recently, a meta-analysis based on nine retrospective studies was published claiming the noninferiority of DNS compared to other conventional cardioplegia solutions. Few prospective randomized studies have been conducted whose primary outcome was the assessment of DNS clinical efficacy compared to other solutions commonly used in adult patients.

**Objective:**

The aim of this randomized clinical trial is to assess the benefits of DNS compared to Cardi-Braun blood cardioplegia solution in clinical and biochemical terms regarding myocardial protection during adult cardiac surgery.

**Methods:**

This is the protocol of a controlled, randomized, single-center clinical trial carried out at the Puerta de Hierro Majadahonda University Hospital in Spain. A total of 474 participants over the age of 18 years undergoing elective cardiac surgery with cardiopulmonary bypass will be assigned to groups by simple randomization to receive either DNS or Cardi-Braun blood cardioplegia solution. The primary outcome will be the differences between groups in myocardial protection in biochemical terms (ie, perioperative troponin levels) and clinical terms (ie, presence of the composite variable *acute cardiovascular event*). The clinical trial will be carried out under conditions of respect for the fundamental rights of the person and the ethical principles that affect biomedical research with human beings, as well as in accordance with international recommendations contained in the Declaration of Helsinki and its subsequent revisions.

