### Trial Design

This study is designed as a single-center, double-blind, controlled clinical trial. Participants will be randomized into a group receiving del Nido cardioplegia (intervention group) or a group receiving Cardi-Braun cold blood cardioplegia (control group; Figure 1). We will conduct a superiority analysis.

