### Outcome Measures

The main variables of the study will be the composite clinical variable *acute cardiovascular event* and the biochemical variable *maximum postoperative troponin value*.

The *acute cardiovascular event* variable will consist of one or several of the following events:

Early perioperative myocardial infarction: occurring during the first 72 hours after surgery and defined according to the criteria of the Task Force of the European Society of Cardiology, the American Heart Association, and the World Heart Federation.Prolonged low cardiac output: defined as the need to maintain support with two or more inotropic and/or other circulatory mechanical assistance devices—intra-aortic balloon counterpulsation (IABC) or extracorporeal membrane oxygenation (ECMO)—beyond the first 24 postoperative hours.Appearance of ventricular arrhythmias: ventricular tachycardia (VT) and ventricular fibrillation (VF) requiring electrical cardioversion in the first 24 postoperative hours.

To analyze the effect of cardioplegia on myocardial protection at a biochemical level, the level of troponins will be monitored upon arrival at the ICU and during the first 48 hours. Likewise, the maximum troponin peak will be collected during the first 48 postoperative hours.

Other secondary variables of efficacy and safety will be analyzed. Among the intraoperative variables, surgical times (ie, ischemia time and cardiopulmonary bypass times), the volume of cardioplegia solution administered and its route of administration, temperature, average blood pressure, and maximum blood glucose values, as well as the need for electrical cardioversion after aortic cross-clamp release, will be monitored.

Among the postoperative variables, the occurrence of atrial fibrillation will be registered, as well as the requirement for inotropic and mechanical pharmacological support, time to withdrawal, and the occurrence of clinical complications (ie, deterioration of ventricular function upon hospital discharge, surgical reintervention, prolonged mechanical ventilation, acute kidney injury, infectious complications, convulsive activity, or stroke). The need for ICU readmission, ICU and hospital length of stay, and mortality will also be noted.

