### Statistical Analyses

#### Sample Size Calculation

The literature reviewed reflects a need for postoperative inotropic vasoactive support ranging from 35% to 40%. In the sample size calculation, we propose that better myocardial protection will be reflected in a lower need for electrical cardioversion, lower pharmacological inotropic or mechanical support, and a lower incidence of myocardial infarction.

For a hypothetical reduction of inotropic support within the first 24 postoperative hours from 38% to 25%, with an α risk of 5%, at a statistical power of 80% (β=.20), by bilateral test with application of the Fleiss correction factor, and estimating losses of 10%, 474 participants distributed into two groups will be necessary.

Participants will be assigned to groups by simple randomization of the sample, obtaining a computer sequence by Stata 16 (StataCorp). The computer distribution will assign 234 participants to the intervention group (DNS) and 240 participants to the control group (blood cardioplegia). When patients arrive at the theater, perfusionists will enroll participants.

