#### Analyses

A description of the data from each group of the study and the total sample will be carried out. The properties of the original variables will be defined, and the aforementioned composite variables will be created. The main variable—*prolonged low cardiac output syndrome*—will be created from the following original variables: *presence of two or more inotropic agents at 24 hours of admission*, *mechanical support with IABC*, and/or *mechanical support with ECMO or other ventricular assistance*. The main composite variable—*acute cardiovascular event*—will be created from the following variables: *perioperative myocardial infarction*, *prolonged low cardiac output syndrome*, *prolonged vasoplegia*, and/or *VT or VF episodes in the first 24 hours*.

The quantitative variables shall be described through the mean (SD), median (IQR), 95% CI, and minimum and maximum values. Qualitative variables shall be presented as relative and absolute frequencies. To ensure the uniformity of the groups, a detailed analysis will be made by evaluating the association using the Pearson correlation coefficient and the *P* value by means of the Student-Fisher *t* test; correction for unequal variances for the quantitative variables, and the association with the odds ratio and the *P* value, will be obtained with chi-square tests for the categorical variables.

The raw effect of each type of cardioplegia on the acute cardiovascular event will be estimated using a logistic regression model.

Two populations will be defined through intention-to-treat analysis and by biological efficacy. The first population will include all the initially randomized subjects, including all those who leave the study due to noncompliance. The second population will include all those subjects who complete the study within the same group in which they were randomized. An intermediate safety analysis will be performed when approximately 50% of patients have been randomized.

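### Two primary outcomes share one two-sided 5% alpha with no rule for success: error is inflated if either suffices, and joint power is not covered if both are required

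*Protocol article*

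**What the plan says.** - **Abstract, Methods:** "The primary outcome will be the differences between groups in myocardial protection in biochemical terms (ie, perioperative troponin levels) and clinical terms", where the clinical term is the acute cardiovascular event composite. One primary outcome, in the singular, is given two contents.
- **Outcome Measures:** "The main variables of the study will be the composite clinical variable" acute cardiovascular event, together with the maximum postoperative troponin value. The troponin peak is collected over the first 48 postoperative hours.
- **Trial Design:** "We will conduct a superiority analysis". It does not say on which outcome.
- **Sample Size Calculation:** "with an α risk of 5%, at a statistical power of 80% (β=.20"), "by bilateral test with application of the Fleiss correction factor". The comparison sized is inotropic support within 24 hours, 38% against 25%, with 10% losses and a total of 474. No other alpha appears in the article.
- **Analyses:** a logistic regression is named for the composite. No between-group test or significance level is named for troponin. Prolonged low cardiac output syndrome is called a main variable and is also listed as a component of the composite. "Two populations will be defined through intention-to-treat analysis and by biological efficacy", without saying which of the two is decisive.

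The article contains no hierarchy, alpha split or statement of whether one or both main outcomes must be positive.

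**The concern.** The primary outcome defines what counts as a positive trial. Here there are two, with one error allowance, so the same data could be read in two ways. If a significant result on either outcome is enough, there are two chances of a false positive and the stated 5% no longer describes the trial. If both are needed, the trial is harder to win than a calculation for a single comparison suggests.

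The distinction matters for this trial in particular. The Conclusions of the abstract and the Discussion argue that earlier prospective studies fell short because their primary objectives were not clinical. Without a rule, a significant troponin difference and a null composite could be reported as a positive primary result, which is the situation the Discussion criticises.

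**Working it through.** **1. What the 5% was spent on.** Inputs from Sample Size Calculation: p1 = 0.38, p2 = 0.25, two-sided alpha 0.05 (z = 1.960), power 0.80 (z = 0.842), Fleiss correction, 10% losses. The mean proportion is 0.315 and the difference d = 0.13.

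- Uncorrected n per arm = [1.960 × √(2 × 0.315 × 0.685) + 0.842 × √(0.38 × 0.62 + 0.25 × 0.75)]² / 0.13² = (1.288 + 0.547)² / 0.0169 ≈ 199.2, so 200.
- Fleiss correction: n′ = (n/4) × [1 + √(1 + 4/(n × d))]² with n = 199.2, which gives about 214.4, so 215.
- Losses: 215 × 1.10 = 236.5, so 237 per arm and **474 in total**, which matches the article. (Dividing by 0.90 instead gives 239 per arm, 478 in total.)

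The stated total therefore comes from one binary comparison at the full two-sided 5%. No alpha was set aside for a second primary test.

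**2. If either outcome suffices.** Let each outcome be tested at two-sided 5%, with no true effect on either.

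- Independent tests, either direction: 1 − 0.95² = 0.0975.
- Independent tests, benefit direction only (2.5% in that tail for each): 1 − 0.975² = 0.0494.
- Correlated tests, bivariate normal with correlation ρ: the either-direction error is 1 − P(|Z1| ≤ 1.96 and |Z2| ≤ 1.96); the benefit-only error is 1 − P(Z1 ≤ 1.96 and Z2 ≤ 1.96), with both statistics signed so that positive means benefit.

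The article gives no correlation between the two test statistics. The range 0 to 0.9 is an assumption.

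| ρ (assumed) | Any false significant difference | False claim of benefit |
|---|---|---|
| 0 | 9.75% | 4.94% |
| 0.3 | 9.5% | 4.8% |
| 0.5 | 9.1% | 4.5% |
| 0.7 | 8.35% | 4.2% |
| 0.9 | 7.0% | 3.5% |
| One test only | 5% | 2.5% |

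Like for like, the inflation runs from 7.0/5 = 1.4-fold to 9.75/5 = 1.95-fold. It is almost the same on the benefit scale (3.5/2.5 = 1.4 to 4.94/2.5 = 1.98).

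**3. If both outcomes are required.** The false-positive rate cannot exceed that of one test, so alpha is not inflated. Joint power cannot exceed the lower of the two individual powers. As an illustration only, suppose each outcome had 80% power: joint power would be 0.80 × 0.80 = 64% if the tests were independent, and would reach 80% only if they always succeeded together. Actual joint power cannot be computed, because the article gives no event rate for the composite and no effect size or SD for troponin.

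**The case against.** The best defence is that the article never says either outcome alone is enough. It joins them with *and*, the abstract speaks of a single primary outcome, the 5% appears only in the sizing, and a model is named only for the composite. On a both-required reading there is no inflation at all. In addition, alpha handling between co-primary outcomes and the choice of decisive population are often left to a statistical analysis plan, which is not shown here.

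Much of this stands. Either-outcome success is one reading of the text, so the error figures are conditional on it. The decisive population, and the looser troponin wording in the abstract, are minor; Outcome Measures does fix the maximum value and the 48-hour window. What does not fall away is that the article itself sets out the primary outcome and leaves the criterion for success open. Each reading has a cost that the sample size section does not account for.

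Some stronger conclusions are tempting but not supported:

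- **A 9% to 10% chance of falsely claiming benefit.** A reader might infer this from the 9.75%. That figure counts false differences in both directions. The test is two-sided, so false benefit is at most 4.9%, against 2.5% for one test.
- **A third primary outcome, with error up to 1 − 0.95³ = 14.3%.** A reader might infer this from the main-variable label on prolonged low cardiac output syndrome. That syndrome is a component of the composite, so the tests cannot be independent and the figure cannot apply.
- **The trial will probably win on troponin alone.** No troponin effect or SD is given, and the Introduction reports that the cited meta-analysis found no significant difference in the evolution of cardiac enzymes.
- **A power cost for splitting alpha, computed from 38% against 25%.** Those rates describe inotropic support within 24 hours, which is neither primary outcome.

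**Conclusion.** The concern holds as a badly fixed success criterion. Two primary outcomes draw on one two-sided 5% alpha that the sample size calculation uses in full for a single binary comparison, and no rule links them.

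The consequence depends on the rule intended. Under an either-outcome rule with 5% on each, the two-sided familywise error is about 7% to 9.75%. Under a both-required rule, error is controlled, but the 80% power claim does not extend to joint success, by an amount the article does not allow one to calculate. The error range rests on bivariate normal test statistics and the assumed correlations. The article does not show that the trial will in fact use an either-outcome rule.

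**What to change.** Before unblinding, and before anyone who sets the rule has seen outcomes by group, state the following:

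1. The acute cardiovascular event composite is tested first, at two-sided 5%, in the intention-to-treat population. This agrees with the clinical primary objective for which the abstract's Conclusions and the Discussion argue.
2. Maximum troponin over 0 to 48 hours is tested at two-sided 5% only if the composite is significant. Otherwise it is reported with its confidence interval and no superiority claim.
3. Prolonged low cardiac output syndrome is described in Analyses as a component of the composite, not as a main variable.
4. The biological-efficacy population is supportive.

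The sequence needs a single definition of the composite. Analyses includes prolonged vasoplegia and Outcome Measures does not, so the two lists must be reconciled at the same time.

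**Cost:** a change of wording. No extra patients are needed, and the composite keeps the full 5%, so it loses no power. The real downside is that a significant troponin result with a non-significant composite could no longer be called a positive primary result.

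Other rules are acceptable if declared in time. If either outcome must be able to carry the claim, a Holm procedure controls the error at some cost in power. If both are meant to be required, the article should say so and give the power for joint success. Putting a figure on either alternative needs a composite event rate and a troponin effect and SD, none of which the article gives.

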**Results:**

The inclusion process started in 2018. Data cleaning and analyses are expected to take place in the fall of 2020 and the results are expected in January 2021.

**Conclusions:**

This study is particularly relevant as it will be one of the first to analyze the clinical effects of del Nido cardioplegia on the basis of direct myocardial protection parameters. In light of published studies, carrying out prospective studies based on primary clinical objectives with a larger sample, high-risk patients, and longer cardiopulmonary bypass times continues to be necessary. We believe that our study addresses an important gap in the knowledge of del Nido cardioplegia in adult patient cardiac surgery and will be able to clarify the possible benefits of this method in a large population of patients undergoing these procedures.

**Trial Registration:**

European Union Drug Regulating Authorities Clinical Trials Database (EudraCT) 2017-005144-14; https://www.clinicaltrialsregister.eu/ctr-search/search?query=2017-005144-14+; ClinicalTrials.gov NCT04094168; https://clinicaltrials.gov/ct2/show/NCT04094168

**International Registered Report Identifier (IRRID):**

DERR1-10.2196/17826

## Introduction

### Scientific Background and Explanation of Rationale

Myocardial protection during cardiac surgery with cardiopulmonary bypass is essential to avoid detrimental effects of ischemia secondary to aortic cross-clamping. To do so, several strategies have been used throughout the years, such as intermittent aortic occlusion, induced ventricular fibrillation, deep systemic hypothermia, or the administration or cardioplegia solutions.

In 1955, Melrose et al were the first to propose the concept of hyperkalemic cardioplegia, using a high-concentration potassium-citrate solution to afford elective reversible cardiac arrest [1]. Ever since, multiple pharmacological solutions and modes of administration have been studied, without currently having a clear and homogenous model considered a reference standard.

On the other hand, there has been a tangible change in the features of patients undergoing cardiac surgery for the last two decades. Patients are older and, therefore, have increased comorbidity, and they undergo more complex surgical procedures, which entail longer ischemia times. The quest for a cardioplegia solution providing maximal myocardial protection has never been more important.

The del Nido cardioplegia solution (DNS) was first formulated for pediatric cardiac surgery in the early 1990s and has been widely used ever since [2]. It contains the crystalloid Plasmalyte, with an electrolyte composition similar to that of the extracellular space. Its mannitol content reduces myocardial cell inflammation and serves as an ischemia induced-free-radical scavenger. Magnesium sulfate improves ventricular recovery by preventing excessive intracellular calcium to build up by blocking calcium channels. The presence of lidocaine, which blocks sodium channels, prolongs the myocyte refractory period. The formula provides adequate myocardial protection for ischemia periods of up to 90 minutes.

Its pharmacological properties have contributed to its popularity for elderly patients with depleted myocardial reserve undergoing cardiac surgery [3,4]. Experimental studies carried out in aged rabbit hearts showed further accumulation of calcium and, therefore, an undermined ventricular function after prolonged ischemic periods. DNS used with the same experimental population showed decreased intracellular calcium levels and fewer spontaneous ventricular contractions [5].

Several retrospective studies have assessed the safety and efficacy of DNS in adults undergoing coronary revascularization, valve replacement, combined procedures, and cardiac reinterventions [6-8].

In 2017, a meta-analysis comparing the effects of DNS and conventional cardioplegia solutions in adult cardiac surgery was published [9]. It concluded that there were shorter aortic cross-clamp times, reduced cardiopulmonary bypass times, reduced need for mechanical ventilation, and shorter intensive care unit (ICU) lengths of stay for the DNS group. On the other hand, no significant differences were observed as far as the following were concerned: the evolution of cardiac enzymes, postoperative vasoactive needs, the appearance of atrial fibrillation, in-hospital lengths of stay, or mortality. DNS appeared to be noninferior in terms of myocardial protection, morbidity, and mortality. Nevertheless, the results are somewhat restricted due to the lack of randomized prospective studies in the analysis.

Recently, two prospective studies assessing the effects of DNS in adults have been published [10,11], yet their primary outcomes focused on myocardial protection indirectly or on biochemical data (ie, electrical activity, need for ventricular defibrillation after the release of the aortic cross-clamp, and troponin evolution after surgery). Light has yet to be shed on the clinical advantages of DNS in adult patients, including older patients and those with a history of ventricular dysfunction.

### Aim of the Study

The aim of this study is to establish the benefits of DNS in clinical and biochemical terms regarding myocardial protection during adult cardiac surgery.

## Methods

### Study Setting

The study was planned according to the updated Consolidated Standards of Reporting Trials (CONSORT) statement, the Declaration of Helsinki, and the Guidelines of Good Clinical Practice issued, as required, by Spanish regulatory authorities. This study will be conducted at one center, the Puerta de Hierro Majadahonda University Hospital.

### Trial Design

This study is designed as a single-center, double-blind, controlled clinical trial. Participants will be randomized into a group receiving del Nido cardioplegia (intervention group) or a group receiving Cardi-Braun cold blood cardioplegia (control group; Figure 1). We will conduct a superiority analysis.

**Figure 1 figure1:**
[figure not shown]
CONSORT flow diagram.

### Eligibility Criteria for Participants

All patients over the age of 18 years who are scheduled for cardiac surgery may be eligible to participate in the study. The inclusion and exclusion criteria are explained in detail in Textbox 1 below.

Inclusion and exclusion criteria for study participants.
**Inclusion criteria**
Patients over the age of 18 yearsPatients undergoing elective cardiac surgery with cardiopulmonary bypass
**Exclusion criteria**
Patients who do not consent to participate in the studyPatients with a documented allergy to amide-type local anestheticsPatients undergoing emergent surgeryUnstable patients who require pharmacological inotropic support; mechanical circulatory support, such as intra-aortic balloon counterpulsation (IABC) or extracorporeal membrane oxygenation (ECMO); or preoperative intubationPatients undergoing mitral valve replacement surgery using the Heartport technique

